## Abstract

**Background:**

Suicide prevention is a national priority for the UK government. Autistic people are at greater risk of experiencing self-harm and suicidal thoughts and behaviours than the general population. Safety plans are widely used in suicide prevention but have not yet been designed with and for autistic people. We developed the first safety plan specifically targeting suicidality in autistic adults: the Autism Adapted Safety Plan (AASP). It consists of a prioritised list of hierarchical steps that can be used prior to or during a crisis to mitigate risk of self-harm and suicidal behaviour. This is a pilot study that aims to assess the feasibility and acceptability of the AASPs and the research processes, including the response rates, potential barriers and reach of AASPs, methods of recruitment, what comprises usual care, and economic evaluation methods/tools.

**Methods:**

This is an external pilot randomised controlled trial of a suicide prevention tool aimed at mitigating the risk of self-harm and suicidal behaviour in autistic adults: AASPs. Participants will be assessed at baseline and followed up 1 month and 6 months later. Assessments include questions about self-harm, suicidality, service use, and their experience of the AASP/taking part in the study. Autistic adults who have a clinical autism diagnosis and self-reported history of self-harm, suicidal thoughts, or suicidal behaviours within the last 6 months will be invited to take part in the study. Informed consent will be obtained. Participants will be recruited via community and third sector services (including community settings, autism charities, and mental health charities). They may also “self-refer” into the study through social media recruitment and word of mouth. Ninety participants will be randomised to either develop an AASP or receive their usual care in a 1:1 ratio.

**Discussion:**

The present study will provide an evaluation of the suitability of the processes that would be undertaken in a larger definitive study, including recruitment, randomisation, methods, questionnaires, outcome measures, treatment, and follow-up assessments.

**Trial registration:**

ISRCTN70594445, Protocol v4: 8/2/22.

**Supplementary Information:**

The online version contains supplementary material available at 10.1186/s40814-023-01264-8.

## Background

Suicide prevention is a national priority for the UK government, and autistic people have recently been identified as a high-risk group in NICE suicide prevention guidelines [1]. Closing the mortality gap between autistic people and the general population is a priority for the Department of Health’s revised 2018 “Think Autism” strategy [2]. Two James Lind Alliance [3] priority setting exercises have highlighted, as an urgent need, research into adapted mental health and suicide prevention interventions for autistic people [4, 5].

Self-harm refers to any act of self-injury or self-poisoning, regardless of suicide intent [6]. Self-harm has traditionally been conceptualised very differently in autism compared to the general population, which has led to this behaviour being overlooked by researchers and clinicians. In autistic people, self-harm has been viewed primarily as a challenging and/or restricted repetitive behaviour characteristic of autism [7, 8] and is often associated with co-occurring intellectual disability [9]. However, in the general population, self-harm is regarded as an indicator of distress and a significant risk marker for later suicide attempts [10]: between 50–60% of those who die by suicide have previously self-harmed [11, 12]. Furthermore, the years of life lost relating to self-harm is estimated to be 30 years [13]. A majority (up to 65%) of autistic adults experience self-harm, as defined in the general population [14, 15], and self-harm is a significant risk marker for suicidal thoughts and behaviours in autistic adults, after controlling for a range of other risk factors (i.e. age, gender, unemployment, mental health problems, and satisfaction with living arrangements) [14]. Autistic people are also significantly more likely to die by suicide than the general population [16, 17]. Identifying and focusing suicide prevention interventions on people who self-harm, regardless of intent, is important for preventing future deaths and a vital element of suicide prevention efforts [18].

Research highlights a lack of appropriate treatment for autistic adults experiencing self-harm, suicidal thoughts, and suicidal behaviours (Camm-Crosbie et al. 2018). Interventions developed for the general population often do not meet the unique needs of autistic people; for example, differences in social communication and camouflaging one’s autistic traits, in order to “fit in” in social situations [19]. Therefore, interventions need to be adapted in order to meet their needs. There is a growing body of evidence for safety planning in the reduction of suicidal behaviour [20] in the general population, but it is not clear whether they are useful in the autistic population. We developed the first safety plan specifically targeting self-harm and suicidality in autistic adults: Autism Adapted Safety Plans (AASP). Safety plans are simple, scalable, and personalisable suicide prevention interventions, with demonstrated effectiveness in a range of clinical interventions [21, 22]. AASPs have the potential for reducing autistic people’s high risk of self-harm and suicide. We plan to conduct an external pilot randomised control trial to assess the feasibility of the AASP for autistic adults.

## Methods/design

### Design

This is an external pilot randomised controlled trial (ISRCTN70594445) of a suicide prevention tool aimed at mitigating the risk of self-harm and suicidal behaviour in autistic adults: AASPs. It is co-produced with autistic people and will focus on an evaluation of the suitability of the processes that would be undertaken in a larger definitive study, including recruitment, randomisation, outcome measures, treatment, and follow-up assessments.

### Aims

In terms of feasibility, we aim to (1) record the proportion of autistic participants who utilise the AASPs; (2) record response rates for completion of outcome measures, follow-up rates, response rates to questionnaires/assessments, and adherence/compliance rates; (3) record time needed to collect and rehearse methods needed to analyse data related to costs and benefits and health impacts; (4) obtain participant and where possible, non-NHS third sector organisations' feedback on suitability and acceptability of AASPs; (5) investigate potential barriers to and reach of the AASPs; (6) obtain feedback from participants and non-NHS third sector organisations on methods of recruitment, randomisation and the proposed outcome measures, possible use of reinforcement activities, research procedures, and data collection methods to inform a definitive trial; and (7) gather information from participants and non-NHS third sector organisations on what comprises usual care to inform a definitive trial. In addition, we will (1) record the number of instances of self-harm and suicidal thoughts and behaviours in a sample of autistic adults (with recent self-harm and/or suicidal thoughts and/or behaviours) in a 6-month period and (2) compare responses to the outcome measures between the intervention and control arm.

### Setting and participants

Up to 90 autistic adults will be recruited via community and non-NHS third sector organisations (including community settings, autism charities, and mental health charities). Autistic adults may self-refer by approaching the research team directly to participate. Autistic adults are eligible if they meet the following criteria: (1) a clinical autism diagnosis; (2) self-reported history of self-harm, suicidal thoughts, or suicidal behaviours within the last 6 months; (3) sufficient spoken English to complete the assessments; and (4) aged 18 + years. Autistic adults are not eligible for study entry if they are currently experiencing psychotic symptoms.

Non-NHS professionals who support autistic adults (e.g. health and social care professionals and charity support workers) will also be recruited through third sector organisations. They will be trained on how to support an autistic person to develop an AASP and along with members of the research team will be available to support those autistic adults randomised to the safety plan arm to develop their plan. The autistic participant will be able to indicate their preference for either a member of the research team or a support worker to assist with the development of their plan.

### Participant identification and recruitment process

The first participant was consented August 11, 2021. Recruitment is planned to continue until October 31, 2022.

Autistic adults will be identified via non-NHS third sector organisations or via self-referral. Non-NHS third sector organisations that have expressed an interest in participation in the study will assist with recruitment in one of two ways, either (a) they will identify potential autistic people accessing their services who meet the inclusion criteria, discuss the study with them, and, if interested, give them a study pack. Interested autistic adults will then complete an expression of interest form that will be sent to the research team. The research team will then contact the potential participants or (b) promote the study to clients through the self-referral route. In the self-referral route, autistic adults may hear about the study through services they are in contact with, via word of mouth, or through promotion on social media. If an autistic person is interested in the study, they will then contact the research team directly. During contact with potential participants, the research team will discuss the study and what participation involves, answer any questions that they may have, and obtain informed consent. Baseline data will then be collected prior to randomisation.

### Measures

The measures recorded as part of the pilot trial are described below, along with the schedule of measurement (Table 1).

**Table 1 Tab1:** Time points at which data are collected

Procedure	Screening	Baseline	1-month follow-up (F1)	6-month follow-up (F2)
**Autistic adults & professionals**				
Eligibility checklist	X			
Informed consent	X			
Wellbeing plan (to note adaptations, participant safety, and emergency contact)	X			
**Autistic adults only**				
Demographics^a^		X		X
MINI		X		
SITBI		X	X	X
VEQ^b^		X	X	X
SBQ-ASC		X		X
EQ-5D-5L		X		X
Resource utilisation questionnaire		X		X
Time and travel questionnaire		X		X
Randomisation^c^		X		
Acceptability and feasibility semi-structured interview for autistic adults				X
SUS^d^				X
CSQ-8^d^				X
**Professionals only**				
Acceptability and feasibility semi-structured interview for professionals				X

^a^Demographics to include — socio-economic status, employment, housing, access to support, physical health, and education

^b^At baseline, this questionnaire asks about their entire life. At F1, it asks about the past month. At F2, it asks about the past 5 months

^c^Randomisation to take place following completion of baseline assessment

^d^Only completed by participants allocated to the AASP arm

#### Baseline characterisation

Mental healthMini-International Neuropsychiatric Interview (MINI; 23): The MINI will be used to assess psychiatric status of participants, including suicidality. It is a short structured diagnostic interview. The MINI is described by the authors as brief and inexpensive, clear and easy to administer, and highly sensitive with good specificity and captures current symptomology [23]. As well as providing diagnostic assessment of suicidality and self-harm, it provides information relating to depression, bipolar I and II, panic disorder, agoraphobia, social anxiety, obsessive–compulsive disorder, posttraumatic stress, alcohol/substance use, psychosis, anorexia nervosa, bulimia nervosa, antisocial behaviours, and generalised anxiety.

#### Feasibility and acceptability outcomes

Acceptability of all aspects of the trial (including outcome measures, acceptability of intervention materials and methods, and any perceived benefits of the AASP) and feasibility (including experience of recruitment and randomisation) are as follows:Bespoke (i.e. developed specifically for the study) acceptability and feasibility semi-structured interview for autistic adults.Bespoke acceptability and feasibility semi-structured interviews with support staff.System Usability Scale (SUS) [24, 25]: Usability of the AASPs for autistic adults will be measured with the SUS. It consists of a 10-item questionnaire with five response options for respondents; from “strongly agree to strongly disagree”. It is easy to administer, can be used on small sample sizes with reliable results, and can validly differentiate between usable and unusable systems. This measure will only be administered to autistic adult participants who developed an AASP.Client Satisfaction Questionnaire-8 (CSQ-8) [26]: This questionnaire is used to assess level of satisfaction with care. It is widely used in mental health settings. Items are scored on a Likert scale from 1 (low satisfaction) to 4 (high satisfaction) with different descriptors for each response point. Total scores range from 8 to 32, with higher scores indicating greater satisfaction. The CSQ-8 has been found to have high internal consistency and concurrent validity in mental health outpatient settings. This measure will only be administered to autistic adult participants who developed an AASP.

Furthermore, to evaluate whether the study is feasible and acceptable and provides sufficient evidence to progress to a definitive trial, we will also record the following:The number of participants who complete the assessments at the 6-month follow-up (primary endpoint)The percentage of participants who rate the usability of the AASPs on the SUS as 68 or above [27], at the primary endpointThe percentage of participants who report satisfaction with the AASP intervention (indicated as a score > 20 on the CSQ-8) at the primary endpoint.Fidelity of delivery to the AASP manual will be undertaken by experts on the delivery of AASPs viewing the session during which the AASP is developed with the autistic adult and rating the session using a bespoke fidelity checklist.

The criterion for progression to be met across sites is that at least 60% of autistic participants approached over the first 4 months of the external pilot consent to be randomised to the study and complete baseline assessments. This will enable us to determine interest from autistic adults in taking part in the study and the potential recruitment rate for a definitive trial. The stop criterion is that if less than 40% of participants randomised attend the AASP sessions, and/or complete the assessments at the primary end point assessment, it is very unlikely that the target could be achieved in a future definitive trial.

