### Randomisation

Participants will be randomised on a 1:1 basis to receive either the AASP + usual care or usual care, without stratification. Randomisation occurs online through sealed envelope (https://www.sealedenvelope.com), facilitated by an unblinded RA who will inform participants of the outcome. Participants will be aware of their randomisation status due to the nature of the intervention.

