### Planned analysis

This external pilot RCT is not powered to estimate a target difference in relative effectiveness but rather to address outcomes to estimate the parameters for a future definitive trial. For pilot studies, a sample size of around 70 participants at endpoint, randomised to treatment vs. treatment as usual, has been recommended to provide sufficient precision to estimate parameters for a full definitive study power calculation [36]; therefore, 90 participants will be recruited to account for drop out.

The feasibility and acceptability outcomes will be analysed using qualitative and descriptive statistics based on mean, standard deviation, median, and interquartile range for continuous data. Number of events and the corresponding percentages will be reported for categorical data. Thematic analysis will be conducted on qualitative feasibility and acceptability interview data. As this is a pilot trial, no formal sample size calculation was performed. However, generalised linear models with appropriate distribution for continuous and categorical data will be used to explore associations between the secondary outcomes and other factors including demographic data. A Bayesian model will be used to estimate the posterior probability that an association between an outcome and a confounder is not the same in the AASP intervention and the usual care groups. For example, if the posterior probability is greater than 60%, we would recommend that such factor is adjusted for a future definitive trial. The external pilot trial will also provide estimates of missing data, which will be calculated as the proportion of participants with outcome data. Using cross-tabulation, we would explore whether participants in the intervention group are more or equally likely to report missing outcome data than those in the usual care group. All data will be analysed under the intention to treat the principle; no interim and no sub-group analysis are planned.

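### Usability, satisfaction and participant acceptability are collected only at 6 months, so people who made a safety plan and left earlier give no rating, and the reported percentages probably overstate acceptability.

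*Protocol article*

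**What the plan says.** In the protocol article, Table 1 (Measures) gives the row "Acceptability and feasibility semi-structured interview for autistic adults" a single mark, in the 6-month (F2) column. The SUS and CSQ-8 rows also have one mark each, in the same column. At the 1-month contact (F1) only the SITBI and VEQ are scheduled.

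Feasibility and acceptability outcomes defines the 6-month follow-up as the primary endpoint. It lists, as evidence on whether to proceed to a definitive trial, the percentage "who rate the usability of the AASPs on the SUS as 68 or above" and the percentage satisfied, "indicated as a score > 20 on the CSQ-8) at the primary endpoint". The text of that section restricts both questionnaires to people who developed an AASP, while the Table 1 footnote restricts them to people allocated to the AASP arm.

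Planned analysis says that "a sample size of around 70 participants at endpoint, randomised to treatment vs. treatment as usual, has been recommended", and "therefore, 90 participants will be recruited to account for drop out". No dropout rate is given. Allocation is 1:1 (Randomisation). The article describes no exit questionnaire and no earlier administration of these measures.

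**The concern.** Acceptability is a main purpose of this pilot. The Aims section asks about the suitability and acceptability of the AASP, about research procedures, and (aim "5) investigate potential barriers to and reach of the AASPs") about what gets in the way of using it. Someone who makes a plan, finds it unhelpful or finds the trial too burdensome, and stops in month 3 has no SUS score, no CSQ-8 score and no interview. Leaving is unlikely to be unrelated to how acceptable the plan or the trial was, so a percentage among those still present at month 6 will tend to be too favourable.

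An analysis plan cannot repair this later. It can add bounds, but it cannot recover ratings that were never collected. The planned cross-tabulation of missing outcome data by arm does not help either, because the SUS and CSQ-8 are given in one arm only.

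**Working it through.** **Inputs from the protocol article:** 90 randomised (Abstract, Methods); about 70 at endpoint (Planned analysis); 1:1 allocation, so about 45 per arm (Randomisation); a stop criterion of 40% for session attendance and/or endpoint completion (Feasibility and acceptability outcomes).

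**Assumptions:** loss is equal in the two arms; everyone allocated to the AASP makes a plan; the response percentages below are illustrative.

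1. *The plan's own figure.* Inflating 70 by N/(1 − d) gives 70/0.80 = 87.5, so 88, at d = 20%, and 70/0.75 = 93.3, so 94, at d = 25%. The stated 90 corresponds to d = 20/90 = 22.2%. This rate is back-solved, so the match at 22.2% confirms nothing independently. It shows only what loss the margin allows for.

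2. *Who is missed.* For the interview (both arms): 90 − 70 = 20 of 90. For the SUS and CSQ-8 (AASP arm only): 45 × 70/90 = 35 scored, 10 of 45 not scored.

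3. *Range for the whole arm.* Suppose 28 of 35 completers (80%) reach the threshold. Counting all 10 leavers as failures gives 28/45 = 62.2%. Counting all as successes gives 38/45 = 84.4%. With 21/35 (60%) the range is 21/45 = 46.7% to 31/45 = 68.9%.

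4. *Sampling error, like for like.* SE = √(0.8 × 0.2/35) = 0.068, and 1.96 × SE = 13.3 points. The 95% interval is about 67% to 93%, a full width of about 26.5 points. The attrition range in step 3 has a full width of 22 points.

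5. *Likely bias rather than extreme bounds.* If a proportion q of the 10 leavers would have met the threshold, the arm value is (28 + 10q)/45:
   - q = 20%: 30/45 = 66.7%, so 80% is 13.3 points too high.
   - q = 40%: 32/45 = 71.1%, so 8.9 points too high.
   - q = 60%: 34/45 = 75.6%, so 4.4 points too high.

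6. *At the edge of the stop criterion.* With 40% completing, 18 of 45 are scored. An observed 14/18 (77.8%) is compatible with 14/45 = 31.1% up to (14 + 27)/45 = 91.1%.

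**The case against.** The AASP is meant for use before or during a crisis, so judging usability after six months of opportunity to use it is a sensible choice. That stands, and F2 should remain the main time point. Retention measures (prompts, a trusted contact) will reduce loss, but they collect nothing from those still lost. Staff interviews, session attendance and fidelity ratings do not depend on the participant's F2 visit. They give partial evidence, though not the participant's own rating.

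Several stronger readings are tempting, and the document does not support them:

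- A reader might infer that 20 of 90 people are missing from the two percentages. The questionnaires go to the AASP arm only, so the figure is about 10 of 45.
- A reader might infer that the plan predicts 22% dropout. It states no rate, and Setting and participants says up to 90.
- A reader might infer that barriers are asked about only at 6 months. The barriers aim names no instrument. The timing is inferred from the interview, and staff are interviewed too.
- A reader might infer that the percentages are defined on completers. No denominator is written and intention to treat is declared, so this is the natural reading only. Denominator rules may also sit in the full protocol or analysis plan.
- A reader might infer that a progression decision would be reversed. The numeric criteria concern consent with baseline completion (60%) and attendance and/or endpoint completion (40%). None uses the SUS or CSQ-8, and heavy attrition is itself a stop criterion.
- A reader might infer that attrition outweighs sampling error. Compared as full widths it does not: 22 against about 26.5 points.

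**Conclusion.** The point holds for the timing of the measures. The SUS, the CSQ-8 and the participant interview are taken once, at F2, so participants who made an AASP and left earlier give no rating. The two percentages then probably overstate acceptability. At the implied 22% loss and an assumed 80% among completers, the overstatement is about 4 to 13 points for assumed leaver success of 60% down to 20%. The bias would shrink if loss were lower, or if leavers rated the plan as stayers do; upward bias is likely, not certain. Using 45 as the denominator ignores people who never make a plan, and their number is unknown.

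The effect is on the acceptability evidence carried into a definitive trial, not on any stated stop rule. The change is worth making because that evidence is a core product of the pilot and the cost is small.

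**What to change.** **Table 1.** Add the SUS and CSQ-8 at the existing F1 contact for all AASP-arm participants who have developed a plan by then, keeping F2 as the main time point. They must go to everyone with a plan, because those who will later stop responding are not known at F1 and cannot be asked at the moment of leaving. Offer a short version of the acceptability interview to participants in either arm who actively withdraw, where contact is appropriate.

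**Feasibility and acceptability outcomes, and Planned analysis.** Report the F2 percentages together with the number who developed an AASP but have no F2 score. Give the F1 result for those people. Add a lower bound that counts them as not reaching the threshold.

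**Cost.** Two schedule entries with a footnote, one or two analysis sentences, and 18 short items (10 SUS, 8 CSQ-8) at a contact that already takes place. Some leavers will decline, ratings at F1 reflect less use of the plan, people lost before F1 are still missed, and the lower bound will look less favourable.

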### Procedure

The baseline measures will be completed before the participants are randomised to the treatment arms. For participants recruited to AASP + usual care who were recruited via non-NHS third sector organisations, a trained support worker from that organisation will complete the AASP with the participant; the participant can then use the AASP as required. Individuals who self-refer will either be paired with a trained support worker from one of the non-NHS third sector organisations or will complete the AASP with a member of the research team, based on their preference. With permission, we will record sessions during which the AASP is completed to enable us to determine fidelity. Based on feasibility study work, we anticipate that completion of the safety plan will take approximately 1 h. The support workers will inform the RAs at each site of the date of completion of the safety plan for each participant. Data consent, data collection, and the development of the AASP may take place remotely via telephone or video call.

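### The stop criterion uses one denominator, all participants randomised, for both AASP attendance and 6-month completion, although only about half of them are offered an AASP

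*Protocol article*

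**What the plan says.** Under Feasibility and acceptability outcomes, the protocol article gives one criterion for progression (consent and baseline completion among those approached) and one for stopping. The stop criterion applies "if less than 40% of participants randomised attend the AASP sessions, and/or complete the assessments at the primary end point assessment". In that event the article judges that a definitive trial would be very unlikely to reach its target.

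The Abstract gives the size and allocation: "Ninety participants will be randomised to either develop an AASP or receive their usual care in a 1:1 ratio". The Randomisation section repeats the 1:1 ratio and names the arms: "Participants will be randomised on a 1:1 basis to receive either the AASP + usual care or usual care".

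The AASP is offered in one arm only. Under Setting and participants, the trained staff "will be available to support those autistic adults randomised to the safety plan arm to develop their plan". The Procedure section says, of participants in the AASP + usual care arm who came through a third sector organisation, that "a trained support worker from that organisation will complete the AASP with the participant". Neither section provides an AASP session for the usual care arm.

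Table 1 schedules the 6-month assessments for all autistic participants. A footnote limits the SUS and CSQ-8 to those allocated to the AASP. The attendance condition carries no such limit.

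**The concern.** One phrase, participants randomised, serves as denominator for two events with different populations at risk. It suits completion of the 6-month assessments, which both arms are due to do. It does not suit attendance at AASP sessions, which only the intervention arm can do. Taken at its word, the attendance condition asks for twice the uptake that the figure of 40% suggests.

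This is the only stop criterion in the article, and informing a definitive trial is the purpose of the pilot. If the sentence is applied literally, good uptake could count as failure. If it is left open and interpreted at the end, the denominator will be chosen by people who have seen the attendance figures.

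**Working it through.** **Inputs.** Stop threshold: below 40% of participants randomised (Feasibility and acceptability outcomes). Total randomised: 90 (Abstract, Methods). Allocation: 1:1, unstratified (Randomisation). Those who can attend: the AASP arm only (Setting and participants; Procedure). The 40% is a chosen cut-off, so there is no derived figure to reproduce.

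**Step 1: arm size.** 90 / 2 = 45, assuming exact balance.

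**Step 2: ceiling on the literal measure.** If every AASP participant attends, 45 / 90 = 50% of those randomised.

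**Step 3: literal rule, with attendance as a separate condition.** The floor is 0.40 × 90 = 36 attenders.
- 36 attenders: 36/90 = 40.0% of all randomised and 36/45 = 80.0% of the AASP arm. The criterion is not met.
- 35 attenders: 35/90 = 38.9% of all randomised and 35/45 = 77.8% of the AASP arm. The criterion is met.

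**Step 4: AASP arm as denominator.** The floor is 0.40 × 45 = 18 attenders.
- 18 attenders: 18/45 = 40.0%. The criterion is not met.
- 17 attenders: 17/45 = 37.8%. The criterion is met.

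**Step 5: where the readings disagree.** From 18 to 35 attenders of 45, or 40.0% to 77.8% of the AASP arm, the literal reading stops and the arm reading does not.

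**Step 6: chance of meeting the attendance condition.** This is exact binomial with n = 45: P(X ≤ 35) for the literal rule and P(X ≤ 17) for the arm rule. The article states no expected attendance, so the true rates are illustrative.

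| True attendance in AASP arm | Literal rule | AASP-arm rule |
|---|---|---|
| 60% | 0.996 | 0.002 |
| 70% | 0.907 | 0.00001 |
| 75% | 0.720 | below 0.00001 |
| 80% | 0.412 | below 0.00001 |
| 85% | 0.127 | below 0.00001 |

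**Step 7: unequal arms.** Suppose 43 to 47 of the 90 fall in the AASP arm (an assumed range). The highest attendance that still meets the literal criterion then runs from 35/43 = 81.4% to 35/47 = 74.5%. The finding does not depend on exact balance.

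**Step 8: the words and/or.** The sentence allows three constructions.
- *Either shortfall is enough.* Steps 2 to 7 then describe when attendance alone stops progression.
- *Both shortfalls are required.* Low attendance alone does not stop; 6-month completion must also be below 40%.
- *One combined count of people who attend, complete, or do both.* Usual care participants who complete then count, the 50% ceiling disappears, and attendance alone does not decide the matter.

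The article does not say which construction applies.

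**The case against.** The strongest reply is that the intended meaning can be recovered. Usual care participants are never offered a session, so attendance makes sense only within the AASP arm. The same section also speaks loosely of a percentage of participants for the SUS and CSQ-8 endpoints, although those instruments go to the AASP arm alone. The stop sentence fits that shorthand. This stands as evidence of intent. It does not repair the sentence, because for the SUS and CSQ-8 the restriction is written down, and for attendance it is not. Nor can participants randomised simply be read as the AASP arm throughout, because the same words govern 6-month completion, for which both arms are the natural denominator.

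A reader might go further and infer that the trial chose an 80% uptake bar, or that attendance up to 79% will certainly trigger a stop. The documents support neither. Nothing suggests that 80% was intended. A stop on attendance alone requires and/or to mean or. With 45 in the arm, 79% cannot occur; the highest value that meets the literal criterion is 77.8%. Nor should the probabilities in the working be called false-stop rates, since that presupposes that 40% of the AASP arm is the intended rule.

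The consequence is also expressed as a judgement about a future trial, alongside usability, satisfaction, fidelity and completion data. No participant's treatment depends on it. That limits the harm, but this is still the one numerical stop rule the pilot offers. Finally, the full protocol is not shown and may name the denominators. If it does, the article needs only to be aligned with it. The point is not that detail is missing: the article states a denominator, and it is unsuitable for one of the two conditions.

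**Conclusion.** The concern holds as a badly specified denominator in a decision rule. Read literally with separate conditions and 45 per arm, attendance is capped at 50% of those randomised, and any AASP-arm attendance below 80% (35 of 45 or fewer) meets the stop criterion. The literal and AASP-arm readings disagree across 18 to 35 attenders of 45, a range wide enough to decide the pilot's conclusion on uptake. The size rests on three assumptions: 90 randomised, near-equal arms, and either condition alone being sufficient. The mismatch of denominators rests only on the allocation ratio and on who is offered an AASP. The AASP-arm reading is probably what was meant, so this is a wording error with a material consequence and not evidence of a deliberately strict threshold.

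**What to change.** Before the criterion is applied, replace the single phrase with a denominator for each condition, keeping attendance as the event:

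- fewer than 40% of participants randomised to the AASP arm attend the AASP sessions;
- fewer than 40% of all participants randomised, in both arms, complete the 6-month assessments.

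Replace and/or with a statement of whether either failure alone is enough to stop or both are needed. That choice belongs to the investigators, but it should be made and dated before attendance and completion are tabulated. If the full protocol already settles these points, cite it and align the article. The cost is one amended sentence, with no extra data, participants or analyses.
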